| Study sample size and statistical considerations: | 
An estimated total sample size of 740 patients (equally distributed between two study arms) will yield 80% power to detect an absolute difference of at least 10% in proportion of patients achieving the primary outcome between two arms using two-sided statistical significance threshold of <math>p=0.05</math>. The estimates in the 'current best practice' group are based on the outcomes of the EXTEND trial where the proportions of LVO patients with the primary outcome (3-month mRS 0-1) were: placebo arm 25%, alteplase arm 28%, with the more conservative assumed proportion taken as 28%. The treatment effect of tenecteplase was based upon the pooled analysis of phase II tenecteplase LVO data where the tenecteplase treatment effect size was 19% greater than alteplase. A more conservative treatment effect of 10% has been assumed for ETERNAL.
 
Adaptive increase in sample size is planned if the result of interim analysis using data from the first 592 patients are promising, as per the methodology of Mehta and Pocock. The maximum sample size is capped at 1000 patients (500 per arm).
 
The primary analysis will be conducted on intention to treat basis. A detailed statistical analysis plan will be formulated before the database lock. The analysis of the primary outcome will be conducted using a modified Poisson regression with excellent functional outcome (mRS 0-1) or return to the pre-morbid mRS as the dependent variable, treatment group as the independent variable and age, NIHSS and onset-to-ECR puncture time (categorized as no ECR, <2 hours, and > 2 hours) as treatment covariates. Secondary and exploratory analyses will be undertaken using appropriate regression models.
 |

## 2. Background

Ischaemic stroke is the leading cause of adult disability in the world. The current standard of care for treatment of patients with acute ischaemic stroke is intravenous recombinant tissue plasminogen activator (tPA, or alteplase), although its use currently remains restricted to less than 4.5 hours from symptom onset. Presently, only 13% of ischaemic stroke patients in Australia receive alteplase, partly due to the time window restriction. Additionally, alteplase performs relatively poorly in patients with a large vessel occlusion (LVO). Despite availability of alteplase, stroke patients with LVO face a devastating outcome due to the large area of brain tissue affected, resulting in >50% of patients dead or highly disabled at 3 months. However, recent trials have shown that endovascular clot retrieval or thrombectomy (EVT) results in at least a doubling of the odds of disability-free survival, compared to treatment with alteplase alone. It is therefore no surprise that there has been worldwide enthusiasm to translate EVT into routine practice. However, endovascular thrombectomy requires considerable operator expertise and infrastructure, so is limited to high volume stroke centres (which also ensures lower complication rates). This means there are inevitable delays in LVO patients receiving EVT, particularly in rural and regional centres, but also in large cities where inter-hospital transfers can be slow. Intravenous thrombolysis given prior to transfer to a thrombectomy capable centre ('drip and ship') may lead to vessel recanalisation in transit and negate the need for thrombectomy. However, alteplase only leads to recanalization prior to thrombectomy in 10% of patients. Further, its use is currently restricted to <4.5 hours after symptom onset.

### **"Tissue is more important than time"**

Although it remains essential to treat acute ischaemic stroke patients with reperfusion therapy (intravenous thrombolysis and/or EVT) as quickly as possible, years of research by our group, and others, have now clearly demonstrated that the treatment window can be safely extended using modern brain imaging. Initially, MRI was used to define salvageable brain tissue (penumbra) and dead brain tissue (ischemic core), but now multimodal CT (incorporating non-contrast CT, CT angiography, and perfusion CT) allows similar assessment of tissue pathophysiology, and is much more accessible around the world, including in rural and regional Australia. Perfusion CT (CTP) is capable of characterizing tissue viability by measuring hemodynamic changes in ischaemic tissue. The ischaemic penumbra can be quantitatively localized on CTP by setting specific physiological cut-offs for the various perfusion maps (also referred to as 'thresholds'). Using these thresholds, it is possible to estimate the volume and location of irreversibility

Protocol Number: UOM2102

Protocol Title: ETERNAL LVO

damaged tissue (the ischemic core) and potentially salvageable ischemic tissue (penumbra). As a result of its ability to positively identify ischemia as well as core and penumbra, CTP has been implemented into routine practice in many centres around the world.

Our group has been integral to the implementation of CTP into routine clinical practice, which has accelerated with specific software applications now being available that automate the processing of perfusion data using validated algorithms and distribute the results via email and picture archiving and communication systems (PACS). Individual reperfusion treatment response is highly variable due to many factors, but the most important predictor of treatment response is how much dead brain (ischemic core) is present, and how much ischemic brain tissue (penumbra) is left to salvage at the time of delivering treatment. If brain tissue is already irreversibly injured, restoration of blood supply will not improve clinical outcome of the individual patient, and reperfusion therapy is futile. There are also potential risks of reperfusion injury when extensive irreversible injury is already established – haemorrhagic transformation and malignant oedema. Multi modal imaging with computed tomography perfusion (CTP) has now been well validated to identify subgroups of patients with varying treatment responses to reperfusion therapy.

[figure not shown]

Figure 1. Using multimodal CT, we have identified three groups whose response to intravenous thrombolysis is quite different. Patients with large established ischemic core do not benefit and may be harmed thrombolysis due to excessive bleeding risk (First row, large ischemic core >70mL). Patients who do not have a large ischemic core but have no significant tissue left to salvage (second row, no mismatch). Finally, patients with a small ischemic core and large penumbra who benefit substantially (third row, target mismatch). These patient groups cannot be differentiated by standard clinical criteria or by non-contrast CT imaging (first column).

Our group has also led the introduction and implementation of automated processing of CTP data (figure 1) to provide real-time ischemic core and penumbral volumes. This technology has already been implemented in many stroke centres around Australia and the world (with our colleagues in the United Kingdom, Spain, Taiwan, Finland, and Canada) and is being used in both routine practice and for clinical trials (TASTE trial).

Following on from validation work by our group, the tissue selection approach using multimodal CT has recently been used to extend the treatment window for endovascular thrombectomy to 24 hours. Additionally, we have recently completed the first trial ever to show that the time window can be extended for intravenous thrombolysis. EXTEND was a randomised double-blind placebo-controlled trial and demonstrated a clinical benefit in patients treated with intravenous alteplase beyond 4.5 hours and up to 9 hours after stroke onset (including 'wake-up stroke'). A crucial element of the EXTEND trial design was imaging selection of patients with a small core and significant volume of penumbra using

Protocol Number: UOM2102

Protocol Title: ETERNAL LVO

automated image processing to standardize interpretation. Together with the DAWN and DEFUSE3 thrombectomy trials, these clinical trials demonstrated that patients do receive benefit from reperfusion treatment in an extended time window *if the patient has a small ischemic core and a significant volume of salvageable brain tissue*.

Although EXTEND was a positive study, the unadjusted absolute benefit of treatment from alteplase in terms of excellent functional outcome at 3 months in the subgroup of patients with large vessel (LVO) patients was very small (25% placebo versus 28%). Similarly, both DAWN and DEFUSE3 had low rates of good 3 month outcome (<20%) in the standard care group (where only 10% of patients received IV thrombolysis due to the late time window). Clearly, outcomes in LVO patients with onset beyond 4.5 hours could be considerably improved upon by a more effective thrombolytic. In terms of patient numbers and potential impact on stroke outcomes, *more than 40% of all referrals for thrombectomy in 2018 to Royal Melbourne Hospital were for patients beyond 6 hours and 66% of patients were transferred to the Royal Melbourne Hospital from regional areas*. Based on current guidelines, none of these patients received IV thrombolysis prior to transfer.

Our group has led the world in testing what appears to be a more effective thrombolytic agent for ischaemic stroke. Tenecteplase (TNK) is a genetically engineered mutant tissue plasminogen activator that has a longer half-life (~22 minutes vs ~3.5min with alteplase, allowing single bolus administration rather than a 1 hour infusion with alteplase), is more fibrin-specific, is more resistant to plasminogen activator inhibitor-1 than alteplase, and does not exhibit the in vitro neurotoxicity that has been observed with alteplase. These pharmacologic and practical advantages make tenecteplase an attractive alternative to alteplase, in particular for inter-hospital transfers. Several trials have already been completed with tenecteplase in acute stroke to provide firm grounding for the treatment dose and establish a safety profile.

After an initial pilot study our group compared 0.9mg/kg alteplase to two doses of TNK (0.10mg/kg and 0.25mg/kg) in a phase II randomised trial that required patients to have a 'dual target' (vessel occlusion on CT angiography and CTP evidence of small core and salvageable brain). The trial demonstrated that treatment with 0.25mg/kg resulted in significantly increased reperfusion at 24 hours and better early neurological recovery, which also translated into improved 3 month outcomes. Of note, this study contained only LVO patients, yet the 24 hour reperfusion rates with TNK were similar to those seen with endovascular thrombectomy in our EXTEND IA study, which was one of the landmark studies leading to EVT becoming the standard of care for LVO stroke.

Figure below

## Reperfusion at 24hr with 0.25 mg/kg TNK

[figure not shown]

The benefit of identifying ischemic tissue and salvageable tissue prior to reperfusion therapy and by excluding mimics using CTP was highlighted by a subsequent phase II tenecteplase trial (ATTEST), which enrolled patients via standard clinical criteria. ATTEST was negative for the primary outcome. Although ATTEST did not use CTP to select patients, fortunately, CTP was still performed. When the ATTEST data was pooled with our Australian TNK trial, only 34% of ATTEST patients had salvageable tissue meeting 'target mismatch' criteria on CTP (explaining the differing results). In the pooled data, there was a substantial clinical benefit over alteplase in patients treated with tenecteplase who had salvageable tissue (return to all usual activities [mRS 0-1] occurred in 35% tenecteplase vs 22% alteplase-treated patients), *with a lower brain haemorrhage rate*.

The recent EXTEND-IA TNK trial, also by our group, showed that 0.25mg/kg tenecteplase was more effective than the standard stroke thrombolytic drug alteplase in patients treated up to 4.5 hours from symptom onset at opening large vessel occlusions prior to thrombectomy in patients who met target mismatch criteria on CTP. The primary outcome of reperfusion at the initial angiogram occurred in 22% of tenecteplase versus 10% of alteplase patients ( $p=0.02$ ). Thus, *1 in 5 LVO patients treated with tenecteplase did not require subsequent thrombectomy* and the number needed to treat with tenecteplase rather than alteplase to prevent one thrombectomy was nine. Although all patients with persisting LVO still went on to thrombectomy, tenecteplase was also associated with improved functional outcome at 90 days (common odds ratio 1.7, 95%CI 1.0-2.8,  $p=0.037$ , Figure 3). This emphasises the benefits of earlier reperfusion with tenecteplase.

**Thrombectomy access in regional areas. 'Drip and ship' in an extended time window.**

Thrombectomy is a highly resource intensive (people and infrastructure) therapy and therefore thrombectomy capable centres are limited to a few metropolitan hospitals in Australia. Direct access to thrombectomy is even more limited worldwide. Given the results of DAWN and DEFUSE3, it is now possible to treat CTP or MR-selected patients up to 24 hours after symptom onset, and thus thrombectomy centres are accepting many more transfer cases than when the treatment window was <6 hours. This is particularly relevant since people living in regional Australia are 19 percent more likely to have a stroke. As part of the transfer protocol, LVO patients within 4.5 hours are given IV alteplase in the regional centre and 'shipped' to a thrombectomy centre. Unfortunately, alteplase performs poorly in this population, as shown in many studies including our recent EXTEND IA TNK trial. Additionally, patients outside the proven 4.5 hours thrombolysis time window are being 'shipped' for thrombectomy without any 'drip'. This means sometimes many hours lapse before recanalization can be achieved via delayed thrombectomy with conversion of penumbra on initial imaging into ischemic core by the time thrombectomy occurs. Notably, our recent EXTEND trial (in which subsequent thrombectomy was not performed) showed only a marginal benefit of alteplase compared to placebo in LVO patients. *The data for tenecteplase compared to alteplase in LVO patients is compelling (early reperfusion prior to angiogram of 10% with alteplase vs 22% with tenecteplase)*, with a higher rate of early reperfusion and corresponding better patient outcomes. However, these data are all from the early time window (<4.5 hours). There is no reason to suspect tenecteplase would not lead to similar improved outcomes if given to patients with target mismatch beyond 4.5 hours. Indeed, the effect may be amplified with longer delays seen between administration of tenecteplase and thrombectomy in regional patients. The reperfusion rates in EXTEND IA TNK reflected treatment at endovascular-capable centres in the majority of patients, with only 25% undergoing inter-hospital transfer within the metropolitan area (median thrombolysis to arterial puncture time 43min). As such, TNK may not have had 'long enough to work'. Our phase II TNK data supports this by showing similar 24 hour reperfusion rates with TNK to endovascular therapy (and considerably superior to alteplase).

### **What about tenecteplase in the 0-4.5 hour window?**

Although both of our previous early time window studies showed a significant benefit of tenecteplase compared to alteplase in terms of 3-month outcome, they were relatively small phase II studies. Our team is running a large phase III trial of tenecteplase versus alteplase (TASTE) which has enrolled over 360 patients (target 700), but it excludes patients with LVO in whom thrombectomy is planned. There is no phase III trial enrolling LVO patients to tenecteplase versus alteplase. Thus, we plan to include LVO patients in the 0-4.5 hour window in ETERNAL. Given the data we have so far, where tenecteplase leads to earlier reperfusion, combined with the low rates of reperfusion with alteplase in LVO, tenecteplase may be particularly beneficial in 'drip and ship' patients where there is a delay between thrombolysis and thrombectomy.

Thus, it is now time to definitively assess tenecteplase in LVO patients in both the early (0-4.5 hours) and delayed (4.5 – 24 hour) time window. ETERNAL LVO will be a phase III trial of treatment with 0.25mg/kg tenecteplase compared to 'standard of care' in patients with a large vessel occlusion and target mismatch on CTP between up to 24 hours after symptom onset. Following publication of our EXTEND trial results we expect there will be some variation in the standard of care for patients with target mismatch in the late time window and anticipate that some clinicians will now wish to give alteplase. However, given that the EXTEND results, as a single trial, may not be sufficient to generate a strong guideline recommendation regarding administration of thrombolysis beyond 4.5 hours, we expect variation in clinical practice in terms of whether 'standard of care' for LVO patients beyond 4.5 hours includes IV alteplase or no thrombolytic. To accommodate this expected variation in practice, the 'standard of care arm' will allow either 0.9mg/kg alteplase or no lytic at the local investigator's discretion, but with the control group treatment pre-specified by the investigator (i.e. alteplase or not) prior to randomisation (covariate adjusted randomisation to minimise imbalances in key prognostic covariates between treatment groups). For example, investigators may be more likely to choose no lytic in patients with larger ischaemic cores (due to perceived risk of ICH), or in those treated in the later part of the 24 hour time window. If not adjusted for at randomisation, this might lead to an imbalance for these variables between the tenecteplase and 'standard of care' groups.

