## **8.4 Randomisation**

Patients will be randomized according to a centralised web-based procedure coordinated via the Melbourne Brain Centre.

The randomization system will be based on computer generated randomization code lists, using a covariate-adjusted randomisation procedure to minimise imbalances on the following covariates: clinician intention to give alteplase or no thrombolysis if randomised to standard of care, age, NIHSS, premorbid mRS, site of Large Vessel Occlusion (Intracranial ICA and M1 vs extracranial ICA and M2, with tandem ICA occlusions to be considered intracranial for the purpose of covariate adjustment) and onset-to-randomization time (0-4.5, 4.5-12 and 12-24 hours, where wake-up stroke/uncertain onset is ‘last seen well within last 24 hours’).

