## 12.3 Sample size

An estimated total sample size of 740 patients (equally distributed between two study arms) will yield 80% power to detect an absolute difference of at least 10% in proportion of patients achieving the primary outcome between two arms using two-sided statistical significance threshold of  $p=0.05$ . The estimates in the 'current best practice' group are based on the outcomes of the EXTEND trial where the proportions of LVO patients with the primary outcome (3-month mRS 0-1) were: placebo arm 25%, alteplase arm 28%, with the more conservative assumed proportion taken as 28%. The treatment effect of tenecteplase was based upon the pooled analysis of phase II tenecteplase LVO data where the tenecteplase treatment effect size was 19% greater than alteplase. A more conservative treatment effect of 10% has been assumed for ETERNAL.

Adaptive increase in sample size is planned if the result of interim analysis using data from the first 592 patients are promising, as per the methodology of Mehta and Pocock. The maximum sample size is capped at 1000 patients (500 per arm)..

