## **12.5 Statistical analysis**

The analysis will be conducted following intention-to-treat principles. All outcomes and analyses are prospectively categorized as primary, secondary or exploratory. Differences in all endpoints between the 2 arms of the study will be tested independently at the two-tailed 0.05 level of significance. All estimates of treatment effects will be presented with 95% confidence intervals. No formal adjustments will be undertaken to constrain the overall type I error associated with the secondary and exploratory analyses. Their purpose is to supplement evidence from the primary analysis to more fully characterise the treatment effect. Results from the secondary analyses will be interpreted in this context. Descriptive statistics will be generated for each of the measures used in study.

The primary outcome will be analysed using modified Poisson regression with modified Rankin Scale (mRS) 0-1 (no disability) or return to pre-morbid mRS at 3 months as the dependent variable, treatment arm as an independent variable, and age, baseline NIHSS score, and randomisation-to-groin puncture time (categorized as no EVT, <2 hours, and >2 hours) as treatment covariates. Treatment effect will be presented as adjusted Risk Ratio with corresponding 95% confidence interval (95%CI).

The analyses of dichotomous secondary efficacy and safety outcomes will be conducted using modified Poisson regression with achieving the respective outcome as the dependent variable, treatment arm as an independent variable, and age, baseline NIHSS score, and randomisation-to-groin puncture time (categorized as no EVT, <2 hours, and >2 hours) as treatment covariates. Treatment effects will be presented as adjusted Risk Ratios with corresponding 95% confidence interval (95%CI).

Protocol Number: UOM2102

Protocol Title: ETERNAL LVO

For the ordinal analysis of the day 90 mRS, an ordinal logistic regression analysis model or an assumption-free Generalized OR model analysis will be undertaken on the full range (0-6) of the scale depending on whether the proportional odds assumption is satisfied.

Exploratory outcome analyses will be carried out according to standard statistical principles for comparison of parametric or non-parametric distributions as appropriate.

The details of the statistical analysis will be summarized in a separate Statistical Analysis Plan prior to the lock of the trial data.

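### Baseline ischaemic core, which the protocol names as an imbalance concern and measures before randomisation, is neither a balancing factor nor a model covariate: a small gain in precision is left unused

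*Protocol*

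**What the plan says.** The Background, in the part on the 0-4.5 hour window, justifies covariate-adjusted randomisation as a way to balance important prognostic variables. It gives two examples: "investigators may be more likely to choose no lytic in patients with larger ischaemic cores", and patients treated late in the 24-hour window. It continues: "If not adjusted for at randomisation, this might lead to an imbalance for these variables". Section 8.1 repeats the argument almost unchanged.

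The balancing factors in section 8.4 are the declared control intention, "age, NIHSS, premorbid mRS, site of Large Vessel Occlusion" and onset-to-randomisation time. The synopsis and sections 4 and 7.1 list the same factors. Core volume is in none of the lists.

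The primary model in section 12.5 adjusts for "age, baseline NIHSS score, and randomisation-to-groin puncture time". The synopsis also uses age, NIHSS and a puncture-time category. Neither includes core.

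Sections 6.1 and 7.1 require each centre to process the baseline images with MiStar before randomisation, because entry depends on a core below 70 mL (section 5 says at or below 70 mL).

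**The concern.** The protocol names two variables at risk of imbalance and acts directly on only one. Onset time is balanced. Core is handled only through its association with the declared control intention, and the primary model does not pick it up afterwards. The protocol itself fixes the balancing list and the primary covariate set, so this is not a detail left to the statistical analysis plan.

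Two things are at stake. A baseline covariate that predicts day-90 outcome beyond age and NIHSS would reduce the standard error of the treatment effect, and the trial already obtains this one to decide entry. And if the arms differ in core by chance, the prespecified estimate will not correct for it, so any correction would be post hoc.

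**Working it through.** **1. The stated sample size.** Section 12.3 gives "placebo arm 25%, alteplase arm 28%, with the more conservative assumed proportion taken as 28" (per cent) for the control group, "A more conservative treatment effect of 10% has been assumed for ETERNAL" for the difference, and "An estimated total sample size of 740 patients (equally distributed between two study arms) will yield 80% power", at two-sided 0.05. With 28% against 38% and a mean of 33%:

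n per arm = [1.960 × √(2 × 0.33 × 0.67) + 0.842 × √(0.28 × 0.72 + 0.38 × 0.62)]² / 0.10² = 346, or 692 in total.

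With the continuity correction, n = (346/4) × [1 + √(1 + 4/(346 × 0.10))]² = 366, or 732 in total, close to 740. The stated figure reproduces and does not depend on core. Without the correction, power at 370 per arm is 82.6%.

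**2. Chance imbalance in core.** In SD units, the standard error of the difference in mean core between two arms of 370 is √(2/370) = 0.0735. The 95% limits are ±1.96 × 0.0735 = ±0.144 SD, and the probability of exceeding 0.1 SD is 17%. Balancing on control intention multiplies these limits by √(1 − ρ²), where ρ is the correlation between core and intention (assumed):

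| ρ | 95% limits (SD) |
|---|---|
| 0.2 | ±0.141 |
| 0.3 | ±0.137 |
| 0.5 | ±0.125 |

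Intention alone therefore narrows chance imbalance in core only slightly.

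**3. Precision from adding core.** The protocol gives no prognostic strength for core, so a range is assumed. Simulated trials (2,500 per row) had 740 patients, 28% against 38%, and modified Poisson regression with robust standard errors. One prognostic score (odds ratio 2 per SD) was already in the model and correlated 0.3 with core. Extra patients = 1/(SE ratio)² − 1, taken before rounding.

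| Core odds ratio per SD | SE with core / SE without | Equivalent extra patients | Power gain (points) |
|---|---|---|---|
| 1 (no effect) | 1.000 | 0% | 0 |
| 0.78 | 0.996 | 0.9% | 0.6 |
| 0.67 | 0.989 | 2.3% | 1.3 |
| 0.55 | 0.977 | 4.9% | 1.6 |
| 0.45 | 0.963 | 7.9% | 2.2 |

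On 740 patients, 0.9% is about 7 and 7.9% about 58. Each power gain carries simulation error of some tenths of a point.

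A second set of 2,000 trials per setting, with odds ratios of 1.25 to 2.0 per SD for smaller core, gave variance ratios of 0.995 to 0.947, that is 0.5% to 5.6% more patients. Power rose by 0.3 to 1.6 points.

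**4. Bias.** In the second set the mean log risk ratio was between 0.304 and 0.312, with or without core. The true value is ln(0.38/0.28) = 0.305. Omitting core does not bias the estimate on average.

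**5. Effect of an imbalance that occurs.** With core omitted, an imbalance at the 0.144 SD limit moved the log risk ratio by about 0.03 to 0.055; a rerun gave nearer 0.02 for the weakest odds ratio, 0.78. Against 0.305 this is about 7% (0.02/0.305) to 18% (0.055/0.305) of the design effect. With core in the model the shift was below 0.01.

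**The case against.** Several stronger readings are tempting, and the documents do not support them.

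- A reader might infer that core-driven choice of control treatment biases the comparison, or that the promised protection is lost. The choice is declared before randomisation, is a balancing factor in every list, and the analysis is by intention to treat. Core-driven choice therefore cannot create a systematic difference between arms. The Background passage is worded as an example and can be read as explaining why intention is balanced. Protection for core is indirect and weak, but not absent.
- A reader might take "the most important predictor of treatment response is how much dead brain (ischemic core) is present" to mean that core is the strongest prognostic factor. The sentence goes on to name remaining penumbra jointly with core, and it concerns response to treatment. Precision depends on prognostic strength for the day-90 outcome beyond age and NIHSS, which the protocol does not quantify. The 70 mL limit also removes the largest cores.
- Open-label treatment does not make this worse. Core is measured before allocation, and allocation is central.
- The trial is not underpowered because of this omission.

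Some of the opposing case stands. The odds ratios are assumptions, and the upper end of the gain needs a strong core effect. The simulations leave out the puncture-time category, so the increment over the exact section 12.5 model was not computed. Chance imbalance is ordinary and already covered by the type I error of the test. Age and NIHSS are legitimate choices, and no passage states that the core value is captured in the database. These points limit the size of the gain. They do not explain why a variable named as an imbalance concern, and already measured, is left out of both lists.

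**Conclusion.** The point holds as one of efficiency and consistency. Core is cited alongside onset time as a variable to protect, yet only time is balanced and neither list contains core. The cost is small: the equivalent of about 0.5% to 8% of patients and about 0 to 2 points of power, for core odds ratios of 0.78 to 0.45 per SD, with nothing lost if core has no effect. Chance imbalance of up to about ±0.14 SD (95% limits) would stay uncorrected in the prespecified estimate. There is no systematic bias, no inflation of the error rate and no wrong figure, and 740 stands. The sizes rest on the assumed odds ratios, the assumed correlation of 0.3 with the variables already adjusted for, and complete core data.

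**What to change.** Before the interim analysis at 592 patients, add baseline MiStar ischaemic core volume to the covariates in section 12.5 and the synopsis, for the primary model and for the secondary and safety models. Enter it as a continuous variable. State in advance the functional form (for example linear or logarithmic), how values from CT perfusion and diffusion MRI are combined, and what is done if a value is missing.

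Reconcile the Background and section 8.1 with the balancing lists in the synopsis and sections 4, 7.1 and 8.4. Either add core to the lists, or reword the rationale to say that declared intention and onset time are balanced and core is adjusted for in the analysis. The second option leaves the randomisation system untouched.

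The cost is one more parameter per model and a check that the core value used for eligibility is captured in the database. The exploratory infarct-growth outcome suggests that it is obtainable. No new measurement is needed and the sample size does not change.
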